### Data management

Data will be entered in the local centres via an Internet-based electronic data capture system which complies with US Food and Drug Administration requirements (21 CFR part 11) and the guidelines of good clinical practice. The data will be stored in a centralised Oracle database (Oracle Corp., Redwood City, CA, USA). The data will be transferred via 128-bit SSL (Secure Sockets Layer) encryption; there will be no local storage of data. The access to the database and webserver is controlled by two consecutive firewall systems. Data will be stored with a pseudonym. The members of the study teams will have access to the electronic data entry system according to a detailed concept of roles and rights. An audit trail ensures an automatic protocol of all data entries, changes, and deletions.

Contact details (e.g., address, telephone number) of the enrolled GPs and patients will be stored separately in electronic files at the study centres in Rostock and Düsseldorf with secure access for the study staff.

### Data analysis

#### Statistical analyses

The analysis of the primary endpoint will be conducted according to the intention-to-treat principle. Sensitivity analyses will be performed on the basis of the per-protocol population (i.e., all patients who have finished the study without any protocol violations will be included in these analyses). Missing values will not be imputed *a priori*. To evaluate a possible bias due to values that are not randomly missing, sensitivity analyses based on multiple imputation will be performed.

Due to cluster randomisation, hierarchic multilevel models (mixed models) with GP practice as a random effect will be applied for the analyses of primary and secondary endpoints. Possible baseline imbalances and confounding variables (e.g., age, sex, co-morbidities) will be controlled by adjustment.

For the evaluation of the primary endpoint, a linear mixed model analysis of variance will be applied.

The analyses of the secondary endpoints will be performed by using linear mixed models or mixed logistic regression models (binary or ordinal), depending of the underlying distribution of the outcome variable.

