This study evaluates the effects of a complex intervention including repeated structured medication reviews and family conferences in frail elderly patients with polypharmacy living at home. The primary hypothesis is that patient safety operationalised as the hospitalisation rate will be reduced in the intervention group compared with the control group with usual care within the study period of 12 months. Secondary hypotheses include that the intervention will reduce the number of prescribed inappropriate drugs, improve health-related quality of life, reduce the rate of falls, and reduce the rate of emergency services. Additionally, we expect that in the intervention group, self-determination of patients will improve and the process of shared decision making between GPs, patients, and family carers will be enhanced.

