#### Primary outcome

The primary endpoint of the study is the number of hospitalisations per patient during the observation period of 12 months. This outcome does not include visits to an outpatient clinic or visits to an emergency unit without hospital admission. The hospitalisations will be documented by the participating GPs after 6 and 12 months and by the patients in their event diary. In case of disparity between the number of hospitalisations documented by GPs and patients, the study centre will be requested to validate the information on hospitalisation. If the information cannot be clarified, the higher value will be used for data analysis.

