### Secondary outcomes

The following secondary outcomes will be analysed on the basis of data collected by study nurses during home visits at baseline and after 6 and 12 months:
Total number of medications, Drug Burden Index defined as the number of anticholinergic and sedative medications [16], prevalence of potentially inappropriate medications (PIMs) [35, 36], medication regimen complexity [37], and drug–drug interactionsWeakness measured by grip strength using a dynamometer (model SH5001; Saehan Corp., Masan, Republic of Korea); best of three attempts usedCognition: Two short cognitive subtests from the Consortium to Establish a Registry for Alzheimer’s Disease neuropsychological test battery, German version, with norms and reliable change indices recently derived from an older German GP sample [38, 39]:
◦ Episodic memory: word list learning (three trials immediate and one trial delayed recall); total administration time: maximum of 10 min plus 10-min interval and approximately 30 s for instruction◦ Executive function: semantic fluency (animal naming test) as a measure of combined verbal ability and executive control; administration time 1 min plus approximately 20 s for instructionDepressive disorder assessed by the Geriatric Depression Scale [40]Mobility measured by the Timed Up & Go Test [41]Health-related quality of life (EQ-5D-5L) will be assessed to facilitate calculation of quality-adjusted life-years (QALYs) for use in the economic analysis [42].Activities of daily living measured by the Barthel index [43]Weight (self-reported)Number of falls (self-reported)Use of emergency services

Detailed procedures of the measurements are listed in the schedule of enrolment, interventions, and assessments (Table 1).

**Table 1 Tab1:** Adapted SPIRIT schedule of enrolment, interventions, and assessments

	Study period						
	Enrolment	Baseline	Intervention				Close-out
Time point	**− t**_**1**_	**t**_**0**_			**t**_**1**_		**t**_**2**_
Month	− 3	0	1	3	6	9	12
Enrolment							
Eligibility screen	X						
Informed consent	X						
Allocation		X					
Interventions							
Intervention group (family conferences)			X	X		X	
Control group (care as usual)							
Assessments							
Hospitalisation rate (NHPP)					X		X
Medication (TNM, DBI, PIM)		X			X		X
Grip strength		X			X		X
Cognition (CERAD)		X			X		X
Depression (GDS)		X			X		X
Mobility (Timed Up & Go Test)		X			X		X
Health-related quality of life (EQ-5D-5L)		X			X		X
Activities of daily living		X			X		X

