Weight		X			X		X
Number of falls		X			X		X
Use of emergency services		X			X		X

*Abbreviations: CERAD* Consortium to Establish a Registry for Alzheimer’s Disease, *DBI* Drug Burden Index, *GDS* Geriatric Depression Scale, *NHPP* number of hospitalisations per patient, *PIM* potentially inappropriate medications, *SPIRIT* Standard Protocol Items: Recommendations for Interventional Trials, *TNM* total number of medications

Participant retention and complete follow-up will be promoted via phone calls by the study nurses. For patients who drop out of the study, the following parameters are requested by the GPs: hospitalisations, cardiovascular events (e.g., stroke, myocardial infarction), mortality, and other adverse events (AEs).

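### The primary model treats every admission count as a full 12-month count, so deaths and unretrieved follow-up that differ between arms can distort the primary comparison

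*Protocol article*

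**What the plan says.** All references are to the protocol article.

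- **Hypothesis (Background).** "The primary hypothesis is that patient safety operationalised as the hospitalisation rate will be reduced in the intervention group".
- **Endpoint (Primary outcome).** "The primary endpoint of the study is the number of hospitalisations per patient during the observation period of 12 months". GPs document admissions at 6 and 12 months, alongside the patient's diary. Table 1 puts the abbreviation for admissions per patient (NHPP) behind the term hospitalisation rate, so the two are the same quantity and neither has a person-time denominator.
- **Model (Statistical analyses).** "For the evaluation of the primary endpoint, a linear mixed model analysis of variance will be applied". For clustering, "hierarchic multilevel models (mixed models) with GP practice as a random effect will be applied". For covariates, "Possible baseline imbalances and confounding variables (e.g., age, sex, co-morbidities) will be controlled by adjustment". Observation time is not among the terms named. For secondary endpoints the choice between linear and logistic models depends on the outcome's distribution; for the primary endpoint the linear model is fixed.
- **Missing data (Statistical analyses).** "Missing values will not be imputed" in the main analysis, which is declared intention-to-treat. Multiple imputation is planned as a sensitivity analysis.
- **Drop-outs (text after Table 1, under Secondary outcomes).** "For patients who drop out of the study, the following parameters are requested by the GPs: hospitalisations", together with mortality and other events. No time window is given.
- **Deaths.** Mortality is documented at 6 and 12 months under Additional safety parameters. The article gives no rule for how a patient who dies before month 12 enters the primary analysis.

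**The concern.** A linear model on the count is sound when every patient is observed for the same 12 months. Here that is doubtful. Patients are 70 or older, at levels 5 to 7 of the frailty scale and care dependent, and only those expected to live 6 months or less are excluded. The Background itself links frailty and polypharmacy to mortality.

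For a patient who dies at month 2, or whose later admissions are never retrieved, the text leaves two routes:

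- The partial count is used. Two months of observation are then read as twelve.
- The patient is treated as missing. The months already observed are lost, and the analysis no longer includes everyone randomised. The multiple-imputation analysis does not repair this for deaths, because it would fill in admissions after death.

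The article uses admissions as its measure of patient safety in a trial of deprescribing. Death prevents further admissions, so an arm with more or earlier deaths would look better on that measure for the wrong reason.

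**Working it through.** **1. The plan's own figure.** Inputs from Sample size: means 0.75 and 0.50, common SD 1.0, power 80%, two-sided alpha 0.05, ICC 0.05, five patients per GP, 10% drop-out.

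- Exact two-sided t test: 253 per group (power 0.801).
- Design effect: 1 + (5 - 1) x 0.05 = 1.2. Total: 2 x 253 x 1.2 = 607.2, rounded up within each arm to 608. Practices: 608 / 5 = 121.6, so 122.
- Drop-out: 608 / 0.90 = 675.6, so 676. Practices: 676 / 5 = 135.2, so 136.

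The figures reproduce. The calculation uses one fixed 12-month count per patient and allows for exits only by enlarging the sample.

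**2. What unequal time at risk does to the count.** Assume exits spread evenly over the year and partial counts used as they stand. With exit proportion d, mean time at risk is 1 - d/2 years, and expected count = annual rate x (1 - d/2). Take the same true rate, 0.75, in both arms. Exit proportions by arm are assumptions; the article gives only 10% drop-out overall.

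| Exits, intervention / control | Mean count, intervention | Mean count, control | Spurious difference | Share of 0.25 |
|---|---|---|---|---|
| 10% / 10% | 0.7125 | 0.7125 | 0.000 | 0% |
| 15% / 10% | 0.6938 | 0.7125 | -0.019 | 7.5% |
| 20% / 10% | 0.6750 | 0.7125 | -0.038 | 15% |
| 20% / 5% | 0.6750 | 0.7313 | -0.056 | 22.5% |

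**3. Other directions, with the planned effect true.**

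- Equal exits of 10%: 0.25 x 0.95 = 0.2375, a dilution of 5%.
- Intervention 10%, control 15%: 0.75 x 0.925 - 0.50 x 0.95 = 0.219. Part of a real benefit is hidden.

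**4. False-positive rate.** Simulation with 4,000 trials per scenario, 68 practices per arm, five patients each, overdispersed counts with SD about 1 and ICC about 0.05. The test is a t test on practice means, which for balanced clusters is equivalent to the planned linear mixed model. True rates are equal; the nominal rate in favour of the intervention is 2.5%.

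| Exits, intervention / control | Raw counts | Admissions per person-time |
|---|---|---|
| 10% / 10% | 2.6% | 2.5% |
| 20% / 10% | 6.1% | 2.3% |
| 20% / 5% | 9.6% | 2.3% |

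With the planned effect and 10% exits in both arms, power is 81.7% for counts and 81.6% for person-time. The case for changing the model is therefore not one of power.

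**5. Deaths linked to frailty.** Steps 2 and 4 assume that exits are unrelated to a patient's admission rate. A further simulation let the risk of death rise with that rate. It assumed mortality of about 17% in the intervention arm and 11% in the control arm, and took overdispersion from the cited 6-month figures: (0.75² - 0.38) / 0.38² = 1.264. With equal true rates and drop-outs' admissions fully retrieved from GPs, raw counts gave -0.036 and 5.6% false positives. Person-time gave -0.012 and 3.3% to 3.5%. With a steeper link between death and frailty, person-time still left about -0.03 and about 5%. An offset therefore reduces this bias without removing it.

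**The case against.** **Drop-out is partly handled.** GPs report admissions independently of the diary, and are asked for them when a patient leaves the study. Ending home visits therefore need not end follow-up for the primary endpoint. This stands, and it matters for size. In the simulation of step 5, with drop-out of 20% versus 10% added, cutting drop-outs off at exit gave -0.064 and 10.8% false positives; full GP retrieval brought this back to -0.036 and 5.6%. A reader might infer that every drop-out shortens the count and quote the larger figures. The article does not support that. What remains is that no window is stated for the retrieval, and that it adds nothing after death.

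**Imbalance is assumed.** The article gives no mortality figure, overall or by arm, and under Quality assurance and safety it says that death is not anticipated. With equal exits there is no spurious effect. A reader might infer that the analysis is built to favour the intervention; it is not, since the direction depends on which arm loses more time. This limits the claim to a vulnerability.

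**Safeguards exist.** Multiple imputation is planned, mortality is recorded, and a monitoring board reviews safety quarterly. Excess deaths would probably be noticed. None of these corrects the primary estimate.

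**Details belong in the analysis plan.** Handling of partial follow-up often does, and that plan is not at hand. The model, however, is fixed in the article. It is fair to add that a mean difference matches the sample-size basis and the cost per admission averted.

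**Rate versus count.** A reader might call this a contradiction. Table 1 equates the two terms, so it is not one.

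**Conclusion.** The point holds in limited form and should be fixed. The article fixes a linear model on a raw 12-month count without time at risk, in a population where some deaths within the year are foreseeable, and neither way of entering those patients is satisfactory.

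The size is moderate. For a 10-point excess of exits in the intervention arm, the false reduction is about 0.04 admissions per patient (15% of the planned effect), with false positives of about 6% instead of 2.5%. This rests on assumed exits of 20% versus 10%, spread evenly over the year, with partial counts used. Full retrieval to month 12 would leave mainly the part due to death. The sample size is unaffected.

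**What to change.** - Make the primary analysis a negative binomial (or Poisson) mixed model with a random intercept for practice and, as offset, the log of days alive and under GP-reported observation, up to 12 months. Include every patient with any follow-up and report the rate ratio.
- State that GP retrieval of admissions for drop-outs runs to month 12 or death, and record the dates of death and of last information.
- Keep the linear mean difference as a supportive analysis; it also serves the cost-effectiveness ratio.
- Report deaths by arm beside the primary result.
- Add one sensitivity analysis that treats death as a terminal event (for example a joint frailty model) or counts it in a composite with admissions. This must accompany the offset, which does not remove bias from death linked to frailty.

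The cost is a change of wording and two dates per patient. The small downside is that the headline measure becomes a rate ratio instead of a difference in means.

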### Sample size

In a similar trial population, the mean rate of hospitalisations amounted to 0.38 per patient with a standard deviation of 0.75 during 6 months [44]. We assume that during an observation period of 12 months, the mean number of hospitalisations per patient will be 0.75 with a common standard deviation of 1.0, and we expect a decrease to a mean number of 0.5 in the intervention group. With a power of 80% and an alpha error of 0.05, we would need a sample size of 253 in each group (two-sided *t* test for equal variances) to detect the expected difference. For a cluster randomised intervention trial, the estimated sample size must be adjusted by the design effect. If an intra-cluster correlation of 0.05 is assumed and about five patients per GP are planned, the design effect would be 1.2 and the sample size would be 608 patients in 122 GP practices. With an estimated drop-out rate of 10% during the study period, 676 patients and 136 GPs will be needed in total.

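### The models listed for secondary endpoints include no count or rate model for falls and emergency-service use, and adjustment for each outcome's own baseline value is not prespecified

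*Protocol article*

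**What the plan says.** Under Statistical analyses, the protocol article gives the model families for secondary outcomes: "The analyses of the secondary endpoints will be performed by using linear mixed models or mixed logistic regression models (binary or ordinal", with the choice to follow the outcome's distribution. GP practice enters as a random effect. The same section says that possible baseline imbalances and confounders will be adjusted for, with age, sex and co-morbidities as examples. Missing values are not imputed in the main analysis.

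The secondary hypotheses at the end of the Background include that the intervention will "reduce the rate of falls, and reduce the rate of emergency services". The Secondary outcomes section lists the number of falls and the use of emergency services among outcomes analysed from data collected by "study nurses during home visits at baseline and after 6 and 12 months". Table 1 schedules both at all three time points, together with medication measures, grip strength, cognition, depression, mobility, quality of life, activities of daily living and weight.

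**The concern.** The list of families is specific, and the article says the distribution decides between them. For an event count observed over a period, the list offers no count or rate family and no term for length of observation. An analyst following it must model the raw count as continuous, treat it as ordinal, or reduce it to a binary outcome. These give different effect measures, and the binary option discards information.

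Time at risk will not be equal. The Sample size section plans for 10% drop-out. Mortality is recorded at 6 and 12 months, and only patients with a life expectancy of 6 months or less are excluded, against 12 months of observation. Falls and health care use come from diaries collected at nurse visits. For drop-outs, the GP is asked for hospitalisations, cardiovascular events, mortality and other adverse events; falls and emergency use are not named. Those counts may therefore end at the last collected diary. A raw count then mixes event rate with length of follow-up, and an analysis of completers discards the partial follow-up.

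The second part concerns precision. An outcome's own baseline value is usually its most informative covariate. Tying adjustment to possible imbalance leaves open whether it is used, and allows that to be decided after the data are seen.

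**Working it through.** **1. The plan's own figure.** The only stated sample size is for the primary endpoint. For the control group the Sample size section assumes that "the mean number of hospitalisations per patient will be 0.75 with a common standard deviation of 1.0". The other inputs there are an intervention mean of 0.5, 80% power and a two-sided 5% t test with equal variances; the stated result is 253 per group.

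- Normal approximation: n = 2 × (1.960 + 0.842)² × 1.0² / 0.25² ≈ 251.2, so 252 per group. The exact t test gives 252.1, so 253.
- Design effect: 1 + (5 − 1) × 0.05 = 1.2. 253 × 1.2 = 303.6, so 304 per group and 608 in total; 608 / 5 = 121.6, so 122 practices. This matches "the design effect would be 1.2 and the sample size would be 608 patients in 122 GP practices".
- Drop-out: 608 / 0.9 = 675.6, so 676; 676 / 5 = 135.2, so 136 GPs.

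All figures reproduce, and nothing below changes them. The article gives no fall rate, dispersion or baseline correlation, so the inputs in steps 2 and 4 are assumptions.

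**2. Count outcomes, simulated.** 400 trials per scenario, 61 practices per arm, 5 patients each; negative binomial counts with a practice effect (SD 0.25 on the log scale); rate ratio 0.7; equal, complete follow-up; cluster-robust marginal models standing in for mixed models; dispersion treated as known in the negative binomial fit.

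| Control mean / dispersion | Linear | Negative binomial | Logistic, any vs none | Loss, logistic vs negative binomial |
|---|---|---|---|---|
| 0.5 / 1 | 0.645 | 0.6475 | 0.4775 | 17.0 points |
| 1.0 / 2 | 0.640 | 0.635 | 0.360 | 27.5 points |
| 1.5 / 3 | 0.5875 | 0.5925 | 0.320 | 27.3 points |

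With no true effect, the rejection rate was 0.05 to 0.0625 (linear), 0.05 to 0.065 (negative binomial) and 0.035 to 0.0525 (logistic). The Monte Carlo standard error is about √(0.6 × 0.4 / 400) ≈ 0.024 for power and √(0.05 × 0.95 / 400) ≈ 0.011 for type I error. Linear and negative binomial are indistinguishable; the loss from dichotomising is far outside simulation error. Ordinal logistic regression was not simulated.

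**3. Time at risk.** The simulation assumed equal follow-up, so it says nothing about the offset. As an illustration, suppose the planned 10% of drop-outs contribute diary data only up to the 6-month visit. Mean observed time is then 0.9 × 12 + 0.1 × 6 = 11.4 months, or 95% of 12. If this is the same in both arms and unrelated to the event rate, a difference in raw means is about 5% too small. If observed time differs between arms, that difference passes directly into the comparison of raw counts.

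**4. Baseline value as covariate.** Residual variance is multiplied by 1 − r², where r is the assumed baseline-to-follow-up correlation. With 253 effective patients per arm (304 / 1.2), the standardised difference detectable at 80% power without a baseline covariate is (1.960 + 0.842) × √(2 / 253) = 0.249. With the covariate it is 0.249 × √(1 − r²).

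| r | Variance factor | Detectable difference |
|---|---|---|
| 0.3 | 0.91 | 0.238 |
| 0.5 | 0.75 | 0.216 |
| 0.7 | 0.51 | 0.178 |
| 0.8 | 0.36 | 0.149 |

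**The case against.** A reader might infer that the baseline values are left out of the models. The text does not say so. The covariates are introduced as examples, imbalance at baseline can include imbalance in the outcome itself, and the Secondary outcomes section makes the baseline visit part of the data to be analysed. A full covariate list is also commonly left to the SAP, which is not shown. This objection stands: what can be said is only that the baseline value is not named and that adjustment is made to depend on possible imbalance. The variance figures compare with a model that ignores baseline altogether, which the article does not commit to. They are also the simple individual-level result; with clustering the gain depends on practice-level correlation too.

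A reader might also infer that the listed models are wrong for counts. That is not supported either. The article uses rate and number per patient interchangeably over a fixed 12 months (it does so for hospitalisation). With complete follow-up, a linear mixed model estimates a difference in mean events per patient-year, and step 2 shows no loss of power or of type I error control. Ordinal regression need not collapse counts, and nothing says that falls will be dichotomised.

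The article being a condensed protocol does not dispose of the count point, because it does state the families and the list has no count or rate model. Nor does the argument for the linear model answer unequal follow-up, on which the section is silent. It is possible that GPs would report some falls as other adverse events for drop-outs, but the article does not say so.

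**Conclusion.** The point holds in a limited form. For two count outcomes hypothesised as rates, the stated families include no count or rate model, and none is said to account for time at risk, although observation time will be unequal. The loss is about 17 to 28 percentage points of power if the counts are dichotomised (assumed control means 0.5 to 1.5, dispersion 1 to 3, rate ratio 0.7), and close to none for a linear model under complete follow-up. Ignoring time at risk has a modest effect if drop-out is 10% and balanced; it cannot be bounded from the article if follow-up differs by arm.

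The baseline covariate is a secondary point about precision. The gain is roughly 9 to 64% of residual variance for assumed r of 0.3 to 0.8, relative to ignoring baseline and before allowing for clustering. Neither part touches the primary endpoint or the sample size.

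**What to change.** For falls and emergency-service use, add to the Statistical analyses section (or fix in the SAP) a mixed negative binomial or Poisson model with a practice random effect and log observation time as offset, with observation time ending at drop-out, death or the last collected diary. State that these counts will not be dichotomised for the main secondary analysis.

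For every secondary outcome measured at baseline, name its baseline value as a prespecified covariate, included whether or not an imbalance is seen.

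The cost is wording and a little more analysis work. The baseline measurements are already planned, and no extra patients or visits are needed. The count outcomes would be reported as a rate ratio rather than a mean difference; the mean difference can be given alongside if readers want an absolute figure.
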